### Patient and public involvement

The initial study idea was conceived by the study team. The patients with KOA, physiotherapists, orthopedist and experts from Shanghai Association of Rehabilitation Medicine took part in preparation of the proposal with face-to-face interviews. In addition, the study protocols also will be modified and supplemented utter concerns not addressed in a draft proposed at the time based on their feedback, to ensure the safety and applicability of the intervention. Furthermore, standardized protocol, technical operations, and clinical applications will also be disseminated through Shanghai Association of Rehabilitation Medicine.

## Discussion

KOA is classified as a peripheral joint disease, but changes in sensation-movement and pain are mediated by the central nervous system. Rasch et al.[53]proved that the muscle weakness caused by osteoarthritis is related to decreased joint function and increased pain, and that quadriceps training can increase muscle strength and relieve joint pain. Patients with KOA often exhibit strength deficiencies [1] and altered neuromuscular control [54] compared to those without KOA, which may result in suboptimal load dissipation within the knee. Though the motor output and pain changes resulting from KOA have been well-studied, the central contribution to muscle activity is less well known. In this protocol, we design four groups to prove the therapeutic role of high-frequency rTMS combined with quadriceps strength training compared to quadriceps strengthen training alone in KOA patients with 12-week intervention and explore changes of brain volume and function connection before and after treatment.

There are only two studies to prove the treatment effect when combined noninvasive brain stimulation (tDCS) with exercise has been publicized [55, 56]. However, the design of the trial was inadequate, which used inappropriate randomization procedures had a small sample size. And the evaluation is only limited to the change of pain in KOA. Thus, we designed a stricter study to explore the dual clinical effects of reducing pain and muscle strength when the neuromodulation of the M1 with high-frequency rTMS combined with quadriceps strength training in KOA. In addition, to the best of our knowledge, this will be the first single-blind study on rTMS in KOA. Moreover, we will also analyze the correlation measurements between the primary outcomes (VAS, TQPEAK) and secondary outcomes (MEP, FC). Furthermore, the study’s exclusion criteria are relatively strict which will exclude many patients. In this case, it is possible to ensure that our experimental results have a certain degree of accuracy and validity.

We recognize this study also has limitations. First, the blinding cannot be performed for the participants and the study operator, because of the visibility of the quadriceps strength training intervention, which might increase the risk of detection bias during the study’s implementation. Second, the exercise training in this protocol is only focuses on quadricep strengthening and not strengthening the whole kinetic chain. Although quadriceps weakness is closely related to the occurrence and development of KOA, strengthening the whole kinetic chain may have greater rehabilitation benefits for KOA than alone quadriceps strengthening. Third, account for the absence of direct evidence on rTMS for improve pain of KOA, we incorporated the effect size of rTMS in alleviating pian of the patients with fibromyalgia in sample size calculation [24]. While there are distinctions between the two types of disease, they both involve central sensitization.

In conclusion, the study will provide evidence to show whether there are synergistic effects following High-Frequency rTMS act on M1 combined with quadriceps strength training and clarify the mechanism of action. The study will help provide rehabilitation prescription recommendations for people with KOA.

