## Abstract

**Background:**

Quadriceps training is necessary in function and activity of daily living for patients with knee osteoarthritis (KOA). However, it did not reduce the rate of surgical treatment for end-stage KOA in the long term. This may be related to brain structure changes and maladaptive plasticity in KOA patients. Transcranial Magnetic Stimulation (TMS) could enhance the functional connectivity of brain regions and improves maladaptive plasticity. However, the synergistic effect of the combination of the two for treat KOA is still unclear. Therefore, the purpose of this study is to investigate whether the High-Frequency rTMS combined with quadriceps strength training can improve the pain and function in KOA more effectively than quadriceps training alone and explore the mechanism of action.

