**Methods:**

This study is an assessor-blind, sham-controlled, randomized controlled trial involving 12 weeks of intervention and 6 months follow-up. 148 participants with KOA will receive usual care management and be randomized into four subgroups equally, including quadriceps strength training, high-frequency rTMS training, sham rTMS and quadriceps strength training, high-frequency rTMS and quadriceps strength training. The rehabilitation interventions will be carried out 5 days per week for a total of 12 weeks. All outcomes will be measured at baseline, 4 weeks, 8 weeks, and 12 weeks during the intervention and 1 month, 3 months and 6 months during the follow-up period. The effectiveness outcomes will be included visual analog scale, isokinetic knee muscle strength, Knee Injury and Osteoarthritis Outcome score and 36-Item Short-Form Health Survey score; The act mechanism outcomes will be included motor evoked potential, grey matter density, white matter, subcortical nuclei volumes, cortical thickness and functional connectivity by MRI. Two-way of variance with repeated measures will be used to test the group and time effect for outcome measures.

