**Discussion:**

The study will be the first protocol to examine whether there are synergistic effects following high-frequency rTMS combined with quadriceps strength training for treat KOA and clarify the mechanism of action. High-frequency rTMS can be added into the training program for KOA patients if it is proven effective.

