Non-invasive brain stimulation is an increasingly growing domain of rehabilitation therapeutics for clinical neurological disorders. A variety of techniques for transcranial brain stimulation has been proposed, such as, Transcranial Direct Current Stimulation (tDCS), Transcranial Magnetic Stimulation (TMS) [19]. A general opinion is that modulation of neuronal excitability by tDCS is a relatively simple function (e.g., cortical excitability is reduced by cathodal stimulation and increased by anodal stimulation) and tDCS effects are difficult to predict, rarely used to treat diseases with various neural circuits, such as, pain related to central sensitization [20]. For rTMS, the magnetic field pulse delivered by a stimulating coil applied on the scalp is able to pass through skull bone without being attenuated and to generate an electric field when entering the brain. The intensity of the induced current is sufficient to produce action potentials and to activate brain networks safely and painlessly [21]. rTMS has been proposed to treat various pain syndromes related to central sensitization phenomenon, a Level A of definite analgesic effect was stated for the use of high frequency rTMS of M1 applied contralaterally to the pain side in patients with neuropathic pain. Previous study demonstrated that the chronic pain associated with KOA may develop in connection with a maladaptive process of pain sensitization in the central nervous system [22]. Hence, there is a basis for speculation that rTMS could be beneficial in alleviating pain associated with KOA.

Although the positive rehabilitation effect of quadriceps strengthening and high-frequency rTMS for KOA have been demonstrated, respectively, the synergistic effect of the combination of the two for treat KOA is still unclear. Therefore, the randomized controlled trial is designed to observe whether high-frequency rTMS combined with quadriceps strength training can better improve the knee function and reduce pain in KOA patients than quadriceps strength training alone and explore the mechanism of this combined rehabilitation. The study will provide a new perspective on the treatment of KOA.

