## Methods

### Study design

This study will be a randomized controlled trial with a parallel-group design. A total of 148 eligible participants will be assigned to the quadriceps strength training (QT group); high frequency rTMS (HT group); sham rTMS and quadriceps strength training (ST + Q group); high frequency rTMS and quadriceps strength training (HT + Q group) at 1:1:1:1 ratio using stratified randomization with gender, age and Kellgren-Lawrence (KL) grade as factors. A brief flowchart of the entire study is shown in Fig. 1 and the schedule of events is provided in Table 1. The study protocol was approved by the Ethics Committee of Shanghai Seventh People’s Hospital (2022-7th-HIRB-065) and registered in the Chinese Clinical Trial Registry (ChiCTR2300067617).

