### QT Group

In the QT group, the participants will receive 20 min quadriceps strength training intervention by using Biodex Multi-Joint System 3 dynamometer (Biodex Medicalt, Shirley, NY, USA). The 12- week intervention duration period has been chosen based on evidence that at least 12 sessions of supervised exercise are required for exercise to be effective in KOA, with a number of studies demonstrating symptom improvement in KOA after 8–12 weeks of exercise [27]. Thus, 12 weeks should be sufficient to show improvement in this population. We will modify the program according to the user’s manual to reduce the risk to participants and check the device for calibration errors. All participants will be informed how the test will be and its purposes. They will conduct two familiarization sessions before the formal intervention to ensure that they feel comfortable during the exercises and perform the technique correctly. After familiarization sessions, participants will be instructed to sit in an isokinetic dynamometer and the V elcro® fixation straps will be tied around the chest, hip and distal thigh of the training limb to prevent compensatory motion from occurring. The dynamometer axis will be aligned with the canter of the lateral femoral condyle. The lever arm will be adjusted according to the training leg length and the resistance will be applied anterior to the ankle joint. The training knee will be kept at a 90° flexed position and they will be instructed to extend knee at angular velocities of 60°/sec, 90°/sec and 120°/sec with 15 repetitions in 3 sets. Rest periods of 30 s between each test extension and 2 min between each velocity will be given. Training will be performed 5 days per week for 12 weeks. A regular physiotherapist will conduct all isokinetic testing with verbal stimuli. Outcome parameters will be assessed by an independent evaluator, who is experienced in handling isokinetic devices [28]. The peak torque (TQPEAK), TQPEAK adjusted for body weight (TQPEAK/BW) and agonist–antagonist (agon/antag) ratio will be the outcomes.

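### The stated efficacy aim compares rTMS plus training with training alone, and the sham comparison that would isolate active stimulation is given no deciding role

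*Protocol article*

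**What the plan says.** The aim appears three times, each time with the same comparator:

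- Abstract, Background: whether the combination "can improve the pain and function in KOA more effectively than quadriceps training alone".
- Background, last paragraph: whether it "can better improve the knee function and reduce pain in KOA patients than quadriceps strength training alone".
- Discussion, first paragraph: the design is meant "to prove the therapeutic role of high-frequency rTMS combined with quadriceps strength training compared to quadriceps strengthen training alone".

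Study design lists quadriceps training (QT) and rTMS alone (HT) as two of the four arms. The other two are "sham rTMS and quadriceps strength training (ST + Q group); high frequency rTMS and quadriceps strength training (HT + Q group) at 1:1:1:1 ratio". QT Group gives the content of the first: "In the QT group, the participants will receive 20 min quadriceps strength training intervention". No sham is part of it.

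The Abstract's Methods calls the study an "assessor-blind, sham-controlled, randomized controlled trial". The Abstract's Discussion draws the practice consequence: "High-frequency rTMS can be added into the training program for KOA patients if it is proven effective".

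Statistical analysis plans a repeated-measures analysis of variance, with Bonferroni-corrected post hoc comparisons where needed. It names and ranks no pair of arms.

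**The concern.** With four arms so defined, training alone describes QT; ST+Q is a separate arm. A trial that met its aim as written would show that HT+Q does better than QT. That difference has several possible sources: active stimulation, the expectation created by coil and noise, and the extra time with staff. The primary effectiveness outcome is a pain VAS that patients mark themselves, and Allocation concealment and blinding says patients are not blind. An effect of expectation or contact is therefore plausible, and a beneficial one would push the result towards rTMS.

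The ST+Q arm separates these sources, but no stated objective or conclusion rests on it. If HT+Q beat QT and matched ST+Q, the written aim would be met and rTMS could be reported as effective although active stimulation had added nothing. This is distinct from the blinding question: perfect blinding between HT+Q and ST+Q would leave the placebo and contact component in HT+Q versus QT.

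**Working it through.** **1. The plan's own figures.** Sample size calculation gives f = 0.24, alpha 0.05, power 0.80, 4 groups and 6 measures, for a total of 116. The correlation among measures is not stated; 0.5 is assumed here.

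- Non-centrality: λ = f²·N·m / (1 + (m − 1)ρ) = 0.24² × 116 × 6 / (1 + 5 × 0.5) = 11.45, with 3 and 112 degrees of freedom. Power is 0.806. The smallest N is 115, or 116 for four equal groups.
- Dropout: 29 / (1 − 0.20) = 36.25, so 37 per arm and 148 in total.

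The stated size reproduces. The point does not depend on it, but it supplies n = 37 (29 completers) per arm.

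**2. What each contrast estimates.** Let A be the effect of active over sham stimulation and S the effect of the sham procedure plus its contact time, both added to training.

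- HT+Q − QT = A + S
- HT+Q − ST+Q = A, if the sham is matched
- ST+Q − QT = S

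The stated aim corresponds to the first line; a claim that stimulation works needs the second.

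**3. Contact time within S.** HT Group states a 20-minute rTMS session. Its parameters give 30 × 4 s + 29 × 40 s = 1,280 s, or 21.3 minutes, which agrees. HT+Q receives this on top of the 20 minutes of training that QT receives. Interventions gives 5 days a week for 12 weeks.

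**4. Size if A = 0.** The documents give neither S nor a VAS SD, so S = d SD is an assumption, shown as a range. The test is a two-sided two-sample t-test at one time point, counting only significant results in favour of HT+Q. The non-centrality is d·√(n/2); at n = 37 and d = 0.5 it is 0.5 × √18.5 = 2.15. The critical t (72 df) is 1.993 at 0.05 and 2.713 at 0.05/6.

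| HT+Q versus QT | d = 0 | 0.2 | 0.3 | 0.5 |
|---|---|---|---|---|
| 37 per arm, Bonferroni over 6 pairs | 0.4% | 4% | 8% | 30% |
| 37 per arm, unadjusted 0.05 | 2.5% | 13% | 25% | 56% |
| 29 per arm, unadjusted 0.05 | 2.5% | 11% | 20% | 46% |

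A simulation of 20,000 trials (37 per arm, unadjusted) gave 13.4%, 24.5% and 56.8% for HT+Q versus QT at d = 0.2, 0.3 and 0.5. For HT+Q versus a matched ST+Q it gave 2.6% to 2.7% at all three.

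**5. On the VAS scale.** Take S as half the protocol's MCID of 1.16, i.e. 0.58 cm, and an assumed SD of 1.5, 2.0 or 2.5 cm. The rates at 37 per arm are 38%, 23% and 17% unadjusted, and 16%, 8% and 5% with Bonferroni.

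**The case against.** A reader might infer that the protocol fixes HT+Q versus QT as the deciding test, so that the trial will declare rTMS effective on the wrong comparison. The document does not go that far:

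- The three statements are narrative aims. Statistical analysis ranks no pair, and its post hoc comparisons could include HT+Q versus ST+Q.
- The Discussion sentence ties the proof to a four-group design, which includes sham.
- The Abstract's Discussion does not say which contrast would count as proof.
- Ranking of contrasts is often left to a statistical analysis plan, which is not shown here.

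HT+Q versus QT is also a legitimate pragmatic question: does adding the whole rTMS package to training help? And the percentages rest on an assumed sham effect and a simple t-test, not the planned repeated-measures analysis. They also presume that a null sham comparison in the same data would be disregarded.

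All of this stands, and it limits the point to the stated aim and the permitted conclusion. It does not remove it. The aim is written, not absent, and it names a comparator that cannot support a claim about active stimulation. An analysis plan that followed it literally would test HT+Q against QT.

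The sham contrast is not automatically clean either. ST + Q Group describes sham given on five days in a row, while Interventions gives 12 weeks for all groups. Allocation concealment and blinding says patients cannot be blind because the training is visible, although both ST+Q and HT+Q include training. Unless the sham is matched and credible, HT+Q versus ST+Q may also carry contact or expectation differences.

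**Conclusion.** The concern holds as a mismatch between the stated aim and the conclusion it is meant to support. HT+Q versus QT is valid for the package as a whole but cannot attribute benefit to active stimulation. The comparison that can do so has no stated deciding role in a trial labelled sham-controlled.

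If stimulation adds nothing and sham plus contact adds an assumed 0.2 to 0.5 SD, HT+Q would significantly outdo QT in about 4% to 30% of trials with Bonferroni over six pairs, against 0.4% nominal in that direction. Unadjusted, the range is 13% to 56% against 2.5%. These rates show what could happen under the assumption; they are not a forecast. The documents do not establish that the planned analysis uses the wrong test, since no pair is fixed. The nominal error rate for HT+Q versus ST+Q presumes a matched sham, which the protocol leaves unsettled.

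**What to change.** - In the Abstract's Background, the Background and the Discussion, name HT+Q versus ST+Q on VAS at 12 weeks as the contrast that decides whether active rTMS adds to training.
- In the Abstract's Discussion, tie the statement about rTMS being shown effective to that contrast, in favour of HT+Q.
- Keep HT+Q versus QT as a secondary, pragmatic comparison of the whole package.
- Report ST+Q versus QT as the estimate of the placebo and contact effect.
- Reconcile ST + Q Group with Interventions on how long sham is delivered, and the statement on patient blinding with the sham design.

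Naming the contrast changes wording only: ST+Q is already randomised at 37 patients, the same number as QT, so precision is unchanged. The reconciliation may take more than wording, depending on what is intended. The downside is that the difference from sham may be smaller than the difference from training alone, so a positive result becomes less likely.

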### Sample size calculation

The sample size was determined based on the priori power analysis through G*Power software version 3.1.9.2. OMERACT-OARSI hip and knee osteoarthritis core outcome set [23] showed that the pain is the most core outcome and the percentage frequency is 94.8% from 1997 to 2017. Furthermore, Guinot et al. [24] reported that the effect size of rTMS for improve pain score in patients with fibromyalgia was 0.24. Therefore, the effect size was set as 0.24 in the present protocol. In the calculations, ANOVA repeated measures between factor was chosen, effect size 0.24, alpha 0.05, power 0.80, number of groups 4, number of measures 6, and the sample size was calculated as 116. Taking into account a conservative anticipation of a 20% drop-out rate, the final sample size will therefore be 37 in each group, with a total of 148 subjects.

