### Interventions

All participants will receive usual care management, including health education and physical therapy when necessary. Six qualified physiotherapists who have attained the physical therapist’s certification with over 5 years of experience will be trained beforehand to instruct and guide patients in carrying out these exercises. The interventions in four groups will be carried out 5 days per week for a total of 12 weeks.

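### The protocol promises evidence on synergy between rTMS and quadriceps training, but no randomised arm lacks both treatments, so the arms can show added benefit only

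*Protocol article*

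**What the plan says.** **The promise.** The Discussion paragraph of the Abstract says the study will "examine whether there are synergistic effects following high-frequency rTMS combined with quadriceps strength training". The last paragraph of the main Discussion repeats it: "the study will provide evidence to show whether there are synergistic effects following High-Frequency rTMS act on M1 combined with quadriceps strength training". The Abstract's Background paragraph and the end of the main Background section also name the synergistic effect of the two treatments as the unanswered question.

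**The purpose sentence.** The sentence that follows in the Background is narrower. It asks whether the combination "can better improve the knee function and reduce pain in KOA patients than quadriceps strength training alone". The Abstract's purpose sentence and the first paragraph of the Discussion use the same comparator.

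**The arms.** The Study design section lists "quadriceps strength training (QT group); high frequency rTMS (HT group); sham rTMS and quadriceps strength training (ST + Q group") and "high frequency rTMS and quadriceps strength training (HT + Q group) at 1:1:1:1 ratio". The Interventions section adds: "All participants will receive usual care management, including health education and physical therapy when necessary".

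**The powered test.** Under Sample size calculation, "ANOVA repeated measures between factor was chosen", with "effect size 0.24, alpha 0.05, power 0.80, number of groups 4, number of measures 6, and the sample size was calculated as 116". The limitations paragraph does not mention synergy, additivity or interaction.

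**The concern.** Two of the four arms, QT and ST+Q, both represent training without active rTMS. HT represents active rTMS without training, and HT+Q represents both. Nobody is randomised to usual care alone, or to sham without training. A two-by-two layout therefore has one empty cell, and it is the cell needed to tell a synergistic effect from a plain sum.

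A finding that HT+Q is better than QT, ST+Q or HT shows that adding one treatment to the other helps. Purely additive effects produce that pattern, and so can effects that partly overlap. If the conclusion keeps its present wording, an ordinary add-on benefit could be read as synergy, which these data cannot support. No analysis plan could repair this, because analysis cannot supply an arm that was not randomised.

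**Working it through.** **1. The plan's own figure.** Inputs from Sample size calculation: f = 0.24, α = 0.05, power 0.80, 4 groups, 6 measures. The correlation between measures is not stated; 0.5 is assumed.

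- λ = f²·N·m / (1 + (m − 1)ρ) = 0.0576 × 116 × 6 / (1 + 5 × 0.5) = 40.09 / 3.5 = 11.45, with 3 and 112 df.
- Power is 0.806 at N = 116 and 0.790 at N = 112, so 116 is reproduced. With ρ = 0.3 the answer would be 84; with ρ = 0.7, 148.
- Dropout: 116 / 4 = 29 per arm; 29 / 0.80 = 36.25, rounded up to 37; 4 × 37 = 148. Reproduced.

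The arithmetic is sound. It powers an overall comparison of four groups, not an rTMS × training interaction.

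**2. What the arms identify.** Let μ be the mean change with neither active treatment, α the effect of rTMS without training, β the effect of training without rTMS, and γ the interaction (synergy if it favours the combination). The arm means are:

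- QT: μ + β
- HT: μ + α
- ST+Q: μ + β (or μ + β + σ if sham has its own effect σ)
- HT+Q: μ + α + β + γ

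The available contrasts are:

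- HT+Q − QT = α + γ (rTMS added to training): estimable
- HT+Q − ST+Q = α + γ, or α + γ − σ (active over sham rTMS, both arms training): estimable
- HT+Q − HT = β + γ (training added to rTMS): estimable
- HT+Q − HT − QT = γ − μ: estimable, but this is not γ

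So γ is known only up to the unobserved μ. A rank check agrees: the design has rank 3 for 4 parameters, or rank 4 for 5 parameters with a sham term, and γ is not estimable in either case. With a neither arm the two-by-two layout has full rank and γ is estimable.

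**3. What this means in centimetres.** Rearranged, γ = (HT+Q) − HT − Q + neither. Assume VAS changes (negative = improvement) of Q −1.5, HT −1.5 and HT+Q −2.5. These are illustrative and not from the protocol. Then γ = −2.5 + 1.5 + 1.5 + neither = 0.5 + neither.

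| Unobserved change, neither arm | γ | Reading |
|---|---|---|
| 0 | +0.5 | less than additive |
| −0.5 | 0 | additive |
| −1.0 | −0.5 | synergistic |

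The three observed means are the same in every row.

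**The case against.** **The word may be meant loosely.** The article never defines synergy and never mentions additivity. In the Abstract, the sentence after the synergy claim is a practical one about adding rTMS to training programmes if it works. On that reading the authors mean only that the combination helps more. This is a fair point, and it shows that the trial is not built on a failed question. It also supports the correction, since the wording should then say added benefit.

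**A large enough combined effect could imply synergy.** If patients on usual care alone do not worsen on average (μ ≤ 0), and HT+Q improves by more than the QT and HT improvements summed, then γ must favour synergy. That is algebraically right. It rests on an assumption that the article does not state and the trial cannot test, and it leaves every smaller combined effect ambiguous. Change from baseline cannot stand in for the missing arm, because it also contains usual care, natural course, placebo response and regression to the mean.

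**Stronger readings to resist.** A reader might infer that the trial's aim as a whole goes unanswered. The documents do not support that: the purpose sentences in the Abstract, Background and Discussion ask whether the combination beats quadriceps training alone, and HT+Q v QT is a randomised comparison that addresses it. Nor does the point show an error in the sample size. It would also be wrong to express the uncertainty as a share of the VAS clinically important difference, since the article gives no figure for change under usual care alone.

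**Conclusion.** The claim in the Abstract's Discussion paragraph and in the closing paragraph of the main Discussion is wrong as written: the design cannot deliver evidence on whether the two treatments are synergistic. That follows from the stated arms by algebra and does not depend on any assumed value. It takes synergy to mean more than the sum of the separate effects, on the scale of mean change.

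The size of the resulting uncertainty cannot be fixed from the document. It equals, centimetre for centimetre, the uncertainty about the mean change under usual care alone; the table above illustrates this and does not estimate it.

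The fault is confined to the synergy claim and to the rationale sentences that pose synergy as the open question. The named comparison with training alone, the comparison with sham plus training and the comparison with rTMS alone all stay available, and the sample-size figure is not in dispute.

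**What to change.** 1. In the Abstract's Discussion paragraph, the closing paragraph of the main Discussion, and the rationale sentences in the Abstract's Background and the main Background, replace synergistic effects with the added benefit that the arms can show:
   - HT+Q v QT, the comparison the protocol itself names;
   - HT+Q v ST+Q, active over sham rTMS when both arms train;
   - HT+Q v HT, training added to rTMS.
2. Add to the limitations that no arm lacks both active treatments, that the rTMS × training interaction is therefore not estimable, and that a positive HT+Q result will not be reported as synergy.

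**Cost.** Wording only. Arms, numbers and data collection stay as they are; the claim becomes narrower.

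If the sponsor does want to test synergy, wording will not be enough: a randomised arm without either active treatment and a prespecified interaction contrast would be needed. The interaction has standard error 2·SD/√n against SD·√(2/n) for a pairwise difference, 1.41 times as large. At 37 per arm, two-sided 5% and 80% power, the detectable interaction is (1.96 + 0.84) × 2/√37 ≈ 0.92 SD, against 0.65 SD pairwise (1.04 against 0.74 SD at 29 per arm; single time point, normal approximation). Narrowing the claim is much the cheaper course.
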